## Abstract

**Introduction:**

The aging of the population and the high incidence of those over 80 lead to an inevitable increase in chronic degenerative diseases, such as dementia, resulting in increased morbidity and disability. Treatment of people with dementia involves both pharmacological and non-pharmacological interventions. In particular, robot-assisted therapy is a potentially useful treatment for dementia as it has the advantage of improving mood, encouraging social interaction and communication. The overall objective of the study is to evaluate the improvement in patient-perceived quality of life following the use of the Paro robot integrated with usual care in the older people with dementia.

**Methods and analysis:**

For this study, 20 patients with dementia are recruited and divided into Experimental Group (EG) and Control Group (CG). Twenty-four session of intervention are conducted, divided into 2 sessions per week, for 12 weeks. The therapy sessions last 20 min. The Experimental Group will receive a social robotic intervention with Paro combined with usual care; the Control Group will receive only the traditional therapy, consisting of cognitive stimulation (reality orientation therapy, cognitive training) and occupational activities (painting workshops, cooking workshops, garden therapy, music therapy, etc.). Paro is a seal-shaped robot designed to have a calming effect and elicit emotional responses in patients in hospitals, nursing homes, and retirement homes. Assessment will be performed at the baseline, at the end of intervention and 3 months after the end of intervention. During these phases, several scales will be administered to the patients, such as Quality of Life—Alzheimer’s Disease, Addenbrooke’s Cognitive Examination, the Rating Anxiety In Dementia scale and the Cornell Scale for Depression in Dementia, Quebec User Evaluation of Satisfaction, Neuropsychiatric Inventory, the Technology Acceptance Model.

**Discussions:**

The final goals of the present study are to evaluate the improvement in patient-perceived quality of life following the use of the Paro robot integrated with usual care in the older people with dementia.

**Ethics and dissemination:**

The study was approved by the Ethic Committee of the Istituto Nazionale Ricovero e Cura Anziani, Istituto di Ricovero e Cura a Carattere Scientifico (IRCCS INRCA) during the session of 12 April 2022. It was recorded in ClinicalTrials.gov on 23 November 2022 on the number NCT05626205. The study findings will be used for publication in peer-reviewed scientific journals and presentations in scientific meetings.

## Introduction

1.

According to data from the 2019 World Population Prospects, the planet’s population is aging: for the first time in history, in 2018 the “over 65 s” globally outnumbered children under the age of 5. In many countries around the world, improved general conditions, progress and socioeconomic well-being have contributed to a steady increase in the older population (1). In Italy, too, a significant demographic change is taking place. ISTAT (Istituto nazionale di statistica) data as of January 1, 2019 reports that the over-65 s number 13.8 million and represent 22.8 percent of the total population (2). The aging of the population and the high incidence of those over 80 lead to an inevitable increase in chronic degenerative diseases, such as dementia, resulting in increased morbidity and disability. Dementia has been defined as a global public health priority according to the World Health Organization and Alzheimer’s Disease International (2016) Report: “in 2010, 35.6 million people were reported to have dementia with estimates of a threefold increase by 2050, with 7.7 million new cases per year (1 every 4 s) and with an average survival, after diagnosis, of 4–8-years” (3). Dementia is the medical term used to refer to a group of degenerative diseases of the brain, usually arising in old age (but not exclusive to the older people), which result in a progressive decline in a person’s cognitive faculties such as memory, language, attention, movement, and the ability to plan and organize. Brain function is impaired to the point of interfering with a person’s normal social and working life. The main feature of dementia is the inability to perform everyday activities as a result of the deterioration of cognitive faculty.

Treatment of people with dementia involves both pharmacological and nonpharmacological interventions, that are recommended as adjunctive treatment.

In recent years, as technology has advanced, robots have been developed to assist the older population, particularly companion robots (4, 5). Two reviews, suggest that robot-assisted therapy is a potentially useful treatment for dementia as it has the advantage of improving mood, encouraging social interaction and communication, assisting individuals with their daily living, improving the well-being of the older people, and decreasing the workload of their caregivers (6, 7). Pet-robot interventions are effective treatment strategies for older people with cognitive impairment and dementia. In addition, these type of patient involvements have been shown to have positive effects on behavioral and psychological symptoms of dementia (8–11).

Social robots have also been used as substitutes for animals in therapy for people with dementia (12). Robots need less space, time or care. Their sensors can respond to environmental changes (movements, sounds…) by simulating interaction with the patient. They can monitor patients or be used in therapy.

Thus, after a review of the literature, among our research objectives is to evaluate the effects of using the newly acquired robotics at our institution (Paro), in patients attending the Alzheimer’s day care center. In fact, numerous studies have indicated that the utilization of Paro has the ability to enhance social interaction among residents, reduce stress and loneliness, and even boost immune system function (13, 14). Additionally, Paro has the potential to enhance both psychological and physiological well-being, and improve overall quality of life (15). These research findings strongly suggest that Paro can offer significant health benefits for older adult(s) individuals. Animal-assisted therapy (16), which integrates animals into human services, health, and education for therapeutic purposes, provides further evidence of the positive impact that Paro could have on the health of older adults. Most previous study tended to investigate the role of Paro in integrated environment including hospitals, homes, long-term care homes. In general, the effects of Paro on older adults in varying aged care facilities require further exploration. Moreover, the use of Paro robotic seal as an intervention has been shown to have a positive impact on various aspects of human well-being. Studies have demonstrated that interacting with Paro can lead to improvements in quality of life, cognitive functioning, and reduction in anxiety and depression. Furthermore, physiological measures of stress have shown a decrease during and after interaction with Paro. The use of Paro as an intervention has also been assessed in the context of job quality, with positive results in terms of job satisfaction and reduced stress levels for those working with older adult(s) or disabled individuals. Overall, the relationship between the intervention with Paro robotic seal and various aspects of human well-being is a promising area of research, with potential for further exploration and implementation in various settings. In particular, PARO has been found to improve social engagement in individuals with dementia, increased activity participation, and promote more spontaneous communication. Moreover, improvements to positive emotions and behaviors in individuals with dementia interacting with PARO has been demonstrated (17–19). PARO has been noted to help individuals become more active, smiling, relaxed and comfortable. In the light of these evidences, our purpose is to investigate, whether the robot can reduce some typical behaviors of the person with dementia (agitation), improve mood and cognitive status, stimulate social interaction, communication, and also reduce the caregiver burden of qualified care-related personnel, and last but not least, the acceptance of technology, compared to traditional treatment in a day care center.

The overall objective of the study is to evaluate the improvement in patient-perceived quality of life following the use of the Paro robot integrated with usual care in the older people with dementia.

## Methods and analysis

2.

### Trial design

2.1.

The study is designed as a pilot single blinded (outcome assessors) randomized controlled trial, with 3-month follow-up, in a group of 20 subjects with dementia, in order to evaluate the improvement in patient-perceived quality of life following the use of the Paro robot integrated with traditional intervention in the older people with dementia. The Experimental Group (EG) will receive a social robotic intervention with Paro combined with traditional one. The Control Group (CG), on the other hand, will receive only the usual care. Assessment will be performed at the baseline (T0), at the end of intervention (after 12 weeks -T1) and 3 months after the end of intervention (follow-up T2).

The primary aim is to evaluate the patient-perceived improvement in terms of quality of life through Quality of Life—Alzheimer’s Disease (QoL-AD), following the use of the Paro robot, integrated with usual care carried out within the IRCCS INRCA Alzheimer’s Day Center.

The Secondary aims are the evaluation of the improvement in cognitive status of the older person with dementia, in terms of orientation, attentional-executive, visuospatial functions, detected through the Addenbrooke’s Cognitive Examination (ACE-R); the assessment of mood improvement in terms of reduction of anxiety and depression, detected through the Rating Anxiety In Dementia (RAID) scale and the Cornell Scale for Depression in Dementia (CSDD); the assessment of the older person’s acceptance of the technology through Quebec User Evaluation of Satisfaction (QUEST 2.0), semi-structured interview and analysis of physiological activation during interaction, with the Noldus Face Reader system and direct observation by the operator; the analysis of behavioral symptomatology through Neuropsychiatric Inventory (NPI); the assessment of practitioner’s acceptance of technology through Technology Acceptance Model (TAM) and the assessment of job quality through semi-structured interview.

### Study setting

2.2.

The study is conducted at the Alzheimer’s Day Center of the IRCCS INRCA, Ancona, Italy. The last version (second version) of the current protocol is dated on 20th April 2022.

### Participants

2.3.

#### Patient characteristics

2.3.1.

The inclusion criteria are:

Diagnosis of mild–moderate dementia according to the Diagnostic and Statistical Manual of Mental Disorders (DSM V).Mini Mental State Examination MMSE between 10 and 24.Signature of informed consent.Age 65 years or older.Have been placed in the Alzheimer’s Day Care Center for at least 3 months.Attending the Alzheimer’s Day Center for at least 6 months.Presence of a caregiver.

The exclusion criteria are:

Sensory disabilities (visual and auditory).Difficulties in comprehension.Failure to meet inclusion criteria.Concurrent participation in other studies.History of syncopal episodes, epilepsy, and dizziness not controlled pharmacologically.Severe autonomic system dysfunction.Severe behavioral syndromes not compensated by medication.Lack of written informed consent.Active implanted and non-implanted medical devices.

#### Operator characteristics

2.3.2.

The inclusion criteria are:

Alzheimer’s Day Center operators (Psychologists, Educators, Social and Health Care Workers with experience within the Alzheimer’s Day Center).

The exclusion criteria are:

Concurrent participation in other studies.Lack of written informed consent.

### Sample size

2.4.

QoL-AD (20) was used to perform a sample size calculation. Assuming an effect size of 35%, the total sample size needed to capture this effect size was estimated to be 16 subjects, assuming a statistical power of 80%, a significance level of 0.05, two groups and 3 repeated assessments (one baseline, 2 follow-ups) in a within-between interactions ANOVA model. Even assuming a drop-out rate of 20%, the total required sample size would be 20 subjects (10 in each arm).

This sample size is assumed to be more than sufficient to capture variation even for secondary outcomes for which treatment effect sizes are assumed to be similar or larger than those identified for the primary outcome.

### Recruitment

2.5.

Patients are selected by the Alzheimer’s Day Center team of the Neurology Operating Unit, IRCCS INRCA, in the Ancona branch. These patients will be contacted by the center manager to schedule an interview with family members. Once they have verified that they meet the inclusion and exclusion criteria of the study and acquired the informed consent in duplicate, signed by both the patient and the family member, the center’s qualified staff will proceed to the baseline assessment with the questionnaires and clinical tests stipulated in the study design. A randomization technique based on a single sequence of random assignments is used. A list of random numbers generated by the computer is used and subject is assigned a number based on their order of inclusion in the study. According to this technique, the subjects are randomly assigned to one of the two study groups. At the end of intervention and after an additional 3 months, the above patients will be evaluated again.

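### Section 2.5 allocates by what reads as simple randomisation, which does not secure the 10 per arm stated in section 2.4

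*Protocol article*

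**What the plan says.** Protocol article, section 2.4 (Sample size), derives the total in two steps. First: "Assuming an effect size of 35%, the total sample size needed to capture this effect size was estimated to be 16 subjects". The inputs it gives for this are 80% power, alpha 0.05, two arms and three assessments, and it names the test as the interaction "in a within-between interactions ANOVA model". Then, allowing for 20% drop-out, "the total required sample size would be 20 subjects (10 in each arm").

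Section 2.5 (Recruitment) describes the allocation: "A randomization technique based on a single sequence of random assignments is used". It continues: "A list of random numbers generated by the computer is used and subject is assigned a number based on their order of inclusion". Neither section mentions blocks, strata, minimisation or a fixed number of labels per arm.

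Section 2.1 (Trial design) calls the study a "pilot single blinded (outcome assessors) randomized controlled trial". Section 2.2 names one day centre as the only site.

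**The concern.** One section states an arm size and the next states an allocation method. Read in its ordinary sense, the method does not deliver that arm size. A single sequence of computer random numbers taken in order of inclusion is the usual description of simple randomisation, under which the arm sizes are themselves random.

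In a large trial the resulting imbalance is negligible in relative terms. With 20 patients it is not: splits such as 7/13 are common, and each one costs precision in the comparison between arms. At stake is some efficiency, and a possible mismatch between the planned and the reported arm sizes.

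**Working it through.** **Inputs.** From section 2.4: 20 randomised, 10 per arm, 20% drop-out, 16 before drop-out, power 80%, alpha 0.05, 2 groups, 3 assessments, within-between interaction. Assumed, because the article does not state them: the 35% effect size is Cohen's f = 0.35, the correlation between assessments is rho = 0.5, and sphericity holds.

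**Step 1: reproduce the plan's figure.** Noncentral F with lambda = f² × N × m / (1 − rho), df1 = (k − 1)(m − 1), df2 = (N − k)(m − 1), where m = 3 and k = 2.

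- N = 16: lambda = 0.1225 × 16 × 3 / 0.5 = 11.76, df = 2 and 28, power 0.837.
- The smallest N with power of at least 0.80 is 15, or 16 with equal arms.
- Drop-out: 16 / (1 − 0.20) = 20.

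The stated 16 and 20 are reproduced.

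**Step 2: arm sizes under simple 1:1 randomisation of 20.** The number in one arm is Binomial(20, 0.5). For example, P(10/10) = 184,756 / 1,048,576 = 0.176. An unequal split multiplies lambda by 4 × n1 × n2 / N².

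| Split of 20 | P(exactly) | P(this or worse) | Factor on lambda | Power, all 20 analysed |
|---|---|---|---|---|
| 10/10 | 0.176 | 1.000 | 1.00 | 0.919 |
| 9/11 | 0.320 | 0.824 | 0.99 | 0.916 |
| 8/12 | 0.240 | 0.503 | 0.96 | 0.907 |
| 7/13 | 0.148 | 0.263 | 0.91 | 0.891 |
| 6/14 | 0.074 | 0.115 | 0.84 | 0.864 |
| 5/15 | 0.030 | 0.041 | 0.75 | 0.821 |
| 4/16 | 0.009 | 0.012 | 0.64 | 0.753 |

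Averaged over all splits, power is 0.902 against 0.919 at 10/10.

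**Step 3: the planned 16 completers.** If drop-out is unrelated to arm, the split of the completers is Binomial(16, 0.5).

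| Split of 16 | P(exactly) | Power |
|---|---|---|
| 8/8 | 0.196 | 0.837 |
| 7/9 | 0.349 | 0.830 |
| 6/10 | 0.244 | 0.811 |
| 5/11 | 0.133 | 0.774 |
| 4/12 | 0.056 | 0.713 |

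P(5/11 or worse) = 2 × (4,368 + 1,820 + 560 + 120 + 16 + 1) / 65,536 = 0.210. Average power over all splits is 0.807.

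**Step 4: the same 16 completers from a 10/10 start.** A restricted list does not guarantee 8/8 after drop-out either, so the fair comparison removes 4 of the 20 at random, giving 4,845 possible sets.

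- 8/8: 45 × 45 = 2,025, or 0.418.
- 7/9: 2 × 10 × 120 = 2,400, or 0.495.
- 6/10: 2 × 210 = 420, or 0.087.

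Nothing worse than 6/10 can occur, so power is never below 0.811. The average is 0.418 × 0.837 + 0.495 × 0.830 + 0.087 × 0.811 = 0.831, against 0.807 under simple randomisation.

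**Step 5: what restriction costs.** If staff know past allocations and the totals, a permutation of 10 + 10 makes on average 9.1% of assignments certain in advance, and a best guess is right 61.7% of the time. Simple randomisation gives 0% and 50%. Fixed blocks of 4 give 33% and 70.8%.

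**The case against.** **The wording may allow a balanced list.** A list prepared with 10 labels per arm is also a single sequence, and section 2.5 does not rule it out. The article condenses a full protocol (second version, cited in section 2.2) that is not shown. This stands as a limit on certainty. It does not remove the point, because the article states a method rather than staying silent, and the natural reading of that method does not yield the stated split.

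**Power hardly suffers on average.** This also stands. The calculation yields a total of 16 and tolerates moderate imbalance. With all 20 analysed, power drops below 80% only at 4/16 or worse, a 1.2% event. With 16 completers the average stays at 80.7%, just above target. For a self-described pilot this is a modest loss.

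**Stronger readings that the article does not support.** A reader might infer that the power calculation requires exactly 10/10, or that a minimum of 8 completers per arm is broken. Section 2.4 sets no per-arm minimum, and 10 per arm appears there only in parentheses. A reader might also infer that the randomisation is invalid. Simple randomisation is valid; the loss is in efficiency.

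**Restriction is not free.** At a single centre where only outcome assessors are blinded, staff can see the allocations and may guess late ones. This stands and shapes the remedy.

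**Conclusion.** The point holds in a moderate form. Followed as worded, section 2.5 misses the split stated in section 2.4 in 82.4% of trials, and in 26.3% it gives 7/13 or worse. These probabilities need only simple 1:1 allocation of 20 patients.

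The power cost averages about 2 to 3 points. The part worth acting on is the tail: with 16 completers, about one trial in five falls to 5/11 or worse and so to 77% power or less, which a 10/10 start excludes if exactly 4 patients drop out.

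The power figures depend on f = 0.35, rho = 0.5, sphericity and drop-out unrelated to arm. The unstated correlation matters: at rho = 0.4 power with 16 in equal arms is already 76.0%, and at rho = 0.6 it is 91.2%. The value 0.5 is used because it reproduces the stated 16. This is an avoidable mismatch that should be corrected; it does not threaten the trial's validity.

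**What to change.** **If randomisation has not begun:** replace the simple sequence with a concealed restricted list. Either a random permutation of 10 EG and 10 CG labels or permuted blocks of varying size will do; the blocks secure 10/10 only if their sizes sum to 20. Someone not involved in recruitment or assessment should hold the list and release assignments one at a time after the T0 assessment. Block sizes should be withheld from recruiting staff.

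**If enrolment has begun:** do not force the remaining places to a final 10/10. After a 9/4 start, for example, the last 7 places would have to be 1 and 6, which is highly predictable and ties allocation to calendar time. If one arm already exceeds 10, a 10/10 total is impossible. Use 1:1 blocks for the remaining places, or report the actual split and restate 10 per arm as an expected split.

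**If a 10+10 list was already used:** one sentence in section 2.5 saying so settles the matter.

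**Cost:** a new computer list, an independent holder and a sentence of text, with no extra patients, visits or measurements. The one real downside is the partial predictability of late assignments, which concealment and undisclosed, varying block sizes limit.

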### Intervention

2.6.

For this study, 20 patients with dementia are enrolled. The study design includes a recruitment phase (R), an initial evaluation phase before the start of treatment (T0), an evaluation at the end of treatment (T1 = 12 weeks from T0), and a follow-up evaluation (T2 = 24 weeks from T0). The Paro use sessions will be 20 min long, including 5 min of introduction to the robot and 15 min of actual use. The intervention will consist of 24 sessions, divided into 2 sessions per week, for the total duration of 12 weeks. The intervention will be considered valid, if individual participants have completed at least 80% of the sessions. Recovery of 2 sessions will be possible. During the treatment, video-recording of the interaction between the patient and Paro is provided, under the supervision of the practitioner.

#### Technological intervention with Paro

2.6.1.

The EG will receive intervention with the PARO robotic animal twice a week. Each session will last 20 min and will be continuous for three months. The meetings will take place in a separate, quiet room. Each session will consist of: (1) welcome of the participant, sanitization of the patient’s hands, presentation of Paro and preparation of the experimental setting involving video-recording of the interaction through camera placed in front of the patient who will be seated without a mask (5 min); (2) free use of Paro by the user (15 min). During the sessions, patients will be asked to dry their hands before interaction with Paro, and instructions will be given on how to avoid mustache contact with the user’s eyes. Throughout the interaction, the operator will maintain a distance of at least 2 m from the patient and wear an FFP2 mask. In addition, the operator will be asked to complete the observer’s checklist (See data collection sheet). Should the patient refuse to interact with Paro, the operator will encourage its use a maximum of 3 times before considering the session void.

The order of sessions, not to exceed 2 sessions per week, will be decided by the practitioner, including the possibility of offering Paro even if the patient manifests agitation or restlessness at any time of the day. Agitation, as assessed by the practitioner, may include verbal aggression, oppositional attitudes, and unrestrained movements. As studies (21–27) have shown, interaction with Paro contributes to mood improvement by helping the caregiver manage restless behavior.

